##### *Criteria for Discontinuation Following Initiation*

1. positive urine toxicology or breath test indicating illicit use of cocaine, amphetamine, alcohol, opiates, or other abused drugs not delivered as part of this protocol;
2. inability to comply with study procedures;
3. meet discontinuation criteria due to exaggerated response to cocaine, described below.

*Rationale for Subject Selection Criteria*

Participants are required to have used cocaine by the IV or smoked route to avoid exposing participants to routes of administration that produce more intensive interceptive effects. The age criteria were selected primarily to avoid enrolling participants with undiagnosed cardiovascular disease. Participants with active HIV disease are excluded to avoid potential exacerbation of their underlying disease; participants with asymptomatic HIV are included because this group is at high risk for cocaine dependence. Participants with asthma (or who take asthma medications) are excluded due to potential adverse interactions between beta agonist medications and cocaine. Patients who heavily use alcohol are excluded due to the potential for disulfiram-alcohol reaction in the several days following completion of the protocol.

*Rationale for genetic assessments.* Data provided by [name] from an ongoing clinical trial shows that disulfiram was superior to placebo on both reported use and positive urine toxicology in patients with the DBH T allele (associated with lower enzyme activity), whereas in patients without the T allele disulfiram was superior to placebo only on reported use measures. Presumably, patients with the T allele have lower baseline DBH activity, and this is more sensitive to inhibition by disulfiram. We elected to allow participants with all DBH genotypes but test for DBH and COMT genotypes and to preferentially include patients with the C/T genotype in an effort to collect data from those most likely to respond to the medication. We will attempt to genotype participants before admission into the GCRC so that beds can preferentially be given to participants with the C/T genotype. Those with the C/C genotype will be enrolled when there is space available.

The infectious disease panel for hepatitis is performed as an aid to determine if the prospective subject has been exposed to a hepatitis virus. Positive hepatitis results do not exclude a prospective subject from participation unless there is an indication of active liver disease. Similarly, a positive tuberculin (PPD) result does not exclude a prospective subject from participation, but if diagnostic tests (e.g. chest x-ray) indicate that active disease is present, subjects may be excluded from participation. If any test results are positive subject will be notified of positive and confirmatory test results by [name] and will be referred for treatment. If positive, they will be referred for appropriate follow-up and/or treatment. [name] will provide subjects with counseling and medical follow-up. They will not be charged for the counseling but you will be responsible for the cost of any medical treatment they need as a result of the diagnosis.

*Payment to Research Participants*

Subjects will be paid $25 in gift certificates to local restaurants and stores for the completion of the initial screening. Subjects may have the option of filling out additional assessments at the end of the initial screen, for an additional $20 in gift certificates.Subjects will receive $30 in gift certificates for completion of the medical screening, including interviews, blood tests, and ECG, which may be scheduled over several days. Subjects will be paid $50 per day, with an additional $100 if they complete the entire study. If they drop out of the study or are excluded at some point, they will be paid according to the number of days participated but the payment date will not change. Payment will occur on the date that would have been the completion date, and the follow up dates two and possibly four weeks later regardless of when the patient leaves the study. Exceptions may be made for participants who are excluded after enrolling in the study but did not choose to leave. Subjects will not receive the entire payment at once, but will be paid according to the following schedule:

Completion of part 1: $100 (cash)

Completion of part 2: $300 (cash)

2-week follow up visit: $300 (cash)

4-week follow up visit: $300 (cash)

For subjects completing the entire study, the total will consist of $1055, of which $1000 will be paid in cash and $55 in gift certificates (or $75 in gift certificates if subjects complete the optional additional screening). Subjects are required to fill out a W-9 form for their payment as part of this study.

Subjects will also have the opportunity to receive money as part of the choice sessions. Across the choice sessions that they participate in, they would be able to receive up to a maximum of $204.80. The actual amount subjects receive will be substantially less because no subject chooses money each time. Subjects must spend the cash earnings prior to being discharged from the GCRC. Study staff will accompany subjects to local stores to make purchases.

**Study Drugs and Dosing Protocols**

*Regulatory issues*. An IND exemption for the use of cocaine and disulfiram in this protocol will be obtained from the FDA. NIDA regulatory staff routinely agrees to provide FDA with a letter granting access to NIDA’s master drug file for cocaine for other projects. Disulfiram is an approved drug and the package insert serves as reference to the master drug file. The PI has a DEA certificate allowing prescription of Schedule II drugs, including cocaine.

*Cocaine.* Human use cocaine HCl in 20mg (10mg/ml in 2ml ampoule) and 40mg (20mg/ml in 2ml ampoule) doses will be provided by a NIDA contractor. The compound will be stored in the UCLA Research Pharmacy vault. Cocaine and matched placebo saline will be administered by IV infusion over at least 60 seconds.

*Study medications.* Disulfiram tablets will be purchased commercially and managed by the Research Pharmacy. The pharmacy will encapsulate the tablets and make matched placebo tables. Participants will take one capsule containing 250mg disulfiram or placebo each morning. The order in which participants receive placebo or disulfiram will be randomized.

*Cocaine dose justification.* In our prior laboratory investigations of effects of cocaine, we have utilized individual doses of 40mg given IV. This dose has been selected to safely produce significant cardiovascular and subjective effects, without reaching a ceiling effect. Maximum doses of 20mg will be used in the choice experiments because the dose will be administered repeatedly, and this dose has been shown to be safe in that context.

**Assessments**

*Genetic Assessments*

*DNA Collection/Isolation.* We will collect DNA from buccal swabs applied to Whatman FTA cards. These cards allow safe and stable storage of biological samples for DNA extraction. Our anticipated yield of genomic DNA is 50-100µg which is adequate for over 500 genotype assays using currently available methods (Del Rio et al 1996; Karle 2001).

*Genotyping.* Genotypes will be determined using 5’ Exonuclease-based (Taqman) genotyping assays. Assays will be developed by Applied Biosystems (ABI; Assays by Design). Allele discrimination will be performed using the ABI 3730 realtime PCR cycler (Geller et al 2004). These procedures will be conducted by the Co-Investigator [name] at UCLA.

*Rationale for genetic assessments*. We elected to test participants for the DBH C/T genotype based on data provided by [name] from an ongoing clinical trial showing that disulfiram was superior to placebo on both reported use and positive urine toxicology in patients with the DBH T allele (associated with lower enzyme activity), whereas in patients without the T allele disulfiram was superior to placebo only on reported use measures. Presumably, patients with the T allele have lower baseline DBH activity, and this is more sensitive to inhibition by disulfiram. We elected to test participants for genotype rather than DBH activity, though the latter is probably more relevant, for two reasons. First, DBH activity is found as a continuum in the population and arbitrary cut-offs would be needed.. Second, the assay for DBH activity is more expensive and less easily performed than the genotyping procedures (at least for our Center).

*Clinical Assessments*

*Addiction Severity Index (ASI)- Lite CF Version*. The ASI-Lite CF version (McLellan et al 1992; McLellan et al 1988) will be administered by a trained research staff member. The ASI-Lite is the interviewer’s estimate of the severity of the participant’s status in seven areas (medical, employment, drug use, alcohol use, legal, family/social, and psychological). The Lite version is a shorter version of the ASI that still retains all questions used to calculate the ASI composite scores. We plan to retain the family history section of the ASI, as the ASI–Lite version collects minimal family history information.

*Substance Use Inventory (SUI).* This instrument collects data on the type, frequency, and amounts of drugs used, as well as routes of administration. Participants will complete this measure during screening to establish severity of drug use for the prior six weeks and at intake to assess drug use during the interval between intake and the time that the SUI was completed during screening.

*Structured Clinical Interview for the DSM-IV (SCID)*. This instrument will be administered during intake screening and serves to determine whether the participant meets the DSM-IV criteria for drug dependence and to rule out any major psychiatric disorders (e.g., affective disorders, schizophrenia) (Spitzer 1995).

*Beck Depression Inventory (BDI).* The BDI is a 21-item self-report inventory that focuses on the participant's subjective feelings of depression and is sensitive to changes over time (Beck et al 1968). Participants will complete the measure during intake screening.

*Medical history and physical exam.* Personal and family health profiles and medical history will be collected prior to the examination and reviewed with a licensed medical professional. A physical exam, neurologic exam, and neuropsychiatric mental status evaluation will be conducted.

*Medical/Pharmacological Assessments*

*Cardiovascular indices*. Beginning 15 minutes before cocaine administration and at 5 to 10 minute intervals thoughout the cocaine administration session, continuing until 240 minutes after the final cocaine administration, blood pressure and heart rate will be monitored using automatic heart rate and blood pressure assessment.

*Clinical laboratory assessment*. Blood for hematology studies will be collected in anticoagulant-containing vacutainer tubes for analysis of CBC, chemistry, liver function tests, and renal function tests. HIV assessment will consist of ELISA with Western-blot confirmation of positive results. A urine-based pregnancy test for females will measure human chorionic gonodotropin.

*Cocaine self-administration procedures.* The participant will indicate the selected option, cocaine or money. For cocaine administration participants will push a button on a PCA pump and will receive the dose immediately.. For delivery of money choices, the research staff will visibly put the money in an envelope designated for the patient for use later on.. Cardiovascular and subjective effects will be assessed prior to and at 5, and 14 minutes after each dose of cocaine. If cardiovascular measures have not returned to acceptable levels (heart rate <130 bpm, diastolic pressure <100mmHg, and systolic pressure <165mmHg), the next choice session will be delayed by 15 minutes, after which these measures will be repeated. These procedures will be repeated for each cocaine self-administration session.

*Cardiovascular monitoring and adverse event management.* We have developed standard operating procedures aimed at allowing safe administration of cocaine in a medical setting. These have been successful, evidenced by our completed and ongoing studies. Participants will be monitored in an ICU-like setting at the Medical Center. An ACLS-certified physician will perform all cocaine administrations and will be present until vital signs have returned to normal. Specific guidelines have been developed to guide assessment and intervention in the event of cardiovascular toxicity, such as malignant hypertension, ventricular arrhythmia, chest pain, etc., and are included in the Appendix. These are intended to support rather than replace clinical judgment. If needed, a “code team” responds. Patients who need to be transferred to a medical or ICU ward can be, though this has never been necessary.

*Stopping Criteria*

Participants must continue to meet inclusion criteria in order to remain in the protocol *(*see criteria for discontinuation following initiation, above.). Thus, cocaine administration will not be initiated if vital signs are outside of acceptable ranges: resting pulse between 50 and 90bpm and blood pressure below 150mm Hg systolic and 90mm Hg diastolic. Repeated doses of cocaine will not be administered (and the study physician will halt continued cocaine delivery by the syringe pump) if any of the following pertain: HR > 130bpm; Diastolic BP > 100mm; Systolic BP > 165mm; Behavioral manifestation of cocaine toxicity (agitation, psychosis, inability to cooperate with study procedures).

*Stopping criteria for further study participation.*  Further participation of the participant is stopped if any of the following events occur: Stopping criteria for further cocaine administration do not return to acceptable limits within 30 minutes; Stopping criteria for further cocaine administration are met for a second time within the protocol; Systolic BP > 180mm Hg sustained for 5 minutes or more; Diastolic BP > 120mm Hg sustained for 5 minutes or more; Heart rate > (220 – age x 0.85) bpm sustained for 5 minutes or more. These are extreme values and we do not anticipate this would occur based on prior experience by ours and other groups administering repeated doses of cocaine in the laboratory.

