*HIV issues.* After informed consent is obtained (described in *Human Subjects*), each participant will undergo HIV testing during their medical screening. A separate consent form for HIV testing provided by UCLA is signed and maintained in the patient’s clinical chart. In the event that any participant tests positive for HIV, he/she will be provided with counseling and medical follow-up. HIV itself is not exclusionary, though the presence of active disease is. Current use of antiretroviral medication is also exclusionary.

*Gender and race/ethnicity.* Participants will be selected without regard to gender or race/ethnicity. The estimates provided are based on our previous experience recruiting research volunteers. Due to the under-representation of women in drug abuse research, we will maximize recruitment of women by targeted advertising. Admission of women will be timed so that cocaine administration occurs during the follicular phase of the menstrual cycle, because cocaine plasma levels are greater then compared to the luteal phase (Lukas et al 1996).

*Participation of children.* Individuals under the age of 21 will not be excluded. Children younger than 18 years old will not be included in the proposed project because cocaine dependence (aside from abuse) is relatively rare in children under 18. The target population for this potential pharmacotherapy is cocaine-dependent adults, so participants for this study will sample from that population (see *Human Subjects*).

*Inclusion Criteria*

In order to participate in the study, participants *must*:

1. Be English-speaking volunteers who are not seeking treatment at the time of the study;
2. Be between 18-55 years of age;
3. Meet DSM IV criteria for cocaine dependence;
4. Have a self-reported history of using cocaine by the smoked or IV route. Participants must report at least weekly use for the past month and have a cocaine-positive urine test in the week of study entry;
5. Have vital signs after a 48 hours washout period as follows: resting pulse between 50 and 90 bpm, blood pressures between 85-150mm Hg systolic and 45-90mm Hg diastolic;
6. Have hematology and chemistry laboratory tests that are within normal (+/- 10%) limits with the following exceptions: a) liver function tests (total bilirubin, ALT, AST, and alkaline phosphatase) < 3 x the upper limit of normal, and b) kidney function tests (creatinine and BUN) < 2 x the upper limit of normal;

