**Experiments**

We propose assess effects of disulfiram and placebo on cocaine self-administration using an established laboratory model. Each participant will complete the experiment during treatment with placebo and disulfiram. The order in which a participant will receive disulfiram or placebo will be randomized to control for order effects.

At 1pm on days 5 and 7, participants will choose between a dose of cocaine (0mg or 20mg) or a monetary alternative in each of 10 subsequent choices. The same dose of cocaine, 0mg or 20mg, will be available for all 10 choices on a given day and each dose will be assigned to either day 5 or 7 in a randomized, double-blind manner. The monetary alternative will be $.05, $.05, $.05, $.05,$1, $4, $7, $10, $13, or $16 cash, presented in that order. Selections will be made at 15-minute intervals, and participants will receive cocaine doses or cash immediately after indicating their choice, providing vital signs remain within preset intervals. Heart rate variability measures will be conducted throughout the choice session as well.

Study drug will be discontinued on day 7, after completion of the experimental sessions. On days 1, 4 and 8, neurocognitive assessments and continous heart rate recording will be completed starting at 3:00 PM. Subjects will be asked to refrain from smoking tobacco for at least 2 hours before the assessment.

Subjects will be monitored through day 8 and on day 9 they can either go home and return to complete the procedures under the alternate condition (placebo vs. disulfiram), or they can stay in the hospital and start the alternate study drug on the next day.

Day 1 Admit to the CRC, complete neurocognitive testing with continuous heart rate recording.

Day 2 *Randomize to study drug 1. The order in*

which participants *receive disulfiram*

*and placebo will be randomized*

Day 3

Day 4 Neurocognitive testing with continuous heart rate recording.

Day 5 Choice session 1

*Participants will choose between cocaine (0mg or 20mg) and money*

Day 6

Day 7 Choice session 2

*Participants will choose between cocaine (0mg or 20mg, reverse of day 5) and money*

Day 8 Monitor. Neurocognitive assessment with continuous heart rate recording.

Day 9 Discharge or subjects can remain in hospital for study part 2

The total possible dose that a patient can receive during choice sessions is 200mg, and the total dose they can receive over the study visit is 200mg.

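### The heart-rate removal rule has its bracket in the wrong place: the 0.85 factor raises the limit above 220 − age, 33 bpm above the probable intent

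*Protocol*

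**What the plan says.** The Protocol's Assessments section sets two tiers of cardiovascular limits for the cocaine sessions.

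- **Dosing halt** (Stopping Criteria). Repeated doses are withheld if "HR > 130bpm; Diastolic BP > 100mm; Systolic BP > 165mm" or if there are behavioural signs of toxicity. Under the self-administration procedures, if measures have not come back to acceptable levels, "the next choice session will be delayed by 15 minutes, after which these measures will be repeated".
- **Removal from the study** (stopping criteria for further study participation). Participation ends if "Stopping criteria for further cocaine administration do not return to acceptable limits within 30 minutes", if "Stopping criteria for further cocaine administration are met for a second time within the protocol", if systolic pressure stays above 180 mm Hg or diastolic above 120 mm Hg for 5 minutes, or on "Heart rate > (220 – age x 0.85) bpm sustained for 5 minutes or more".

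The text adds of the removal limits: "These are extreme values and we do not anticipate this would occur based on prior experience". It gives no worked heart-rate value and does not state the formula a second time. The age criterion is "Be between 18-55 years of age".

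**The concern.** With the bracket around the whole expression, 0.85 multiplies age and nothing else. A factor below 1 in a safety limit would be expected to tighten it. Here it shrinks the amount subtracted from 220 and so raises the limit. Staff applying the rule have no printed bpm value against which to notice this.

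The rule governs when a participant leaves the study during repeated intravenous cocaine. If the limit is too high, someone whom the 5-minute rule was probably meant to remove stays in and may be offered further doses. The point concerns participant safety. It does not touch sample size, power or alpha.

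**Working it through.** **Inputs**

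- Removal limit as printed: 220 − 0.85 × age, sustained for 5 minutes (stopping criteria for further study participation).
- Eligible ages: 18 to 55 (Inclusion Criteria).
- Dosing halts: heart rate 130 bpm, systolic 165, diastolic 100 (Stopping Criteria).
- Blood-pressure removal limits: systolic 180, diastolic 120 (stopping criteria for further study participation).
- Choices per session and dose: 10 choices, at most 20 mg each (Experiments).

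The plan states no bpm figure, so there is none to reproduce.

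**Step 1: three versions of the limit (bpm)**

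| Age | Printed: 220 − 0.85 × age | Factor removed: 220 − age | Bracket moved: 0.85 × (220 − age) |
|---|---|---|---|
| 18 | 204.7 | 202 | 171.7 |
| 30 | 194.5 | 190 | 161.5 |
| 40 | 186.0 | 180 | 153.0 |
| 55 | 173.25 | 165 | 140.25 |

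**Step 2: effect of the factor as printed.** (220 − 0.85 × age) − (220 − age) = 0.15 × age. That is 2.7 bpm at 18, 4.5 at 30, 6.0 at 40 and 8.25 at 55. It is positive at every eligible age, so the factor always raises the limit.

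**Step 3: gap to the probable intent.** 0.85 × (220 − age) = 187 − 0.85 × age. The difference from the printed limit is 220 − 187 = 33 bpm, whatever the age.

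**Step 4: which form fits the other tiers.** From dosing halt to removal, systolic rises by 180 − 165 = 15 mm Hg and diastolic by 120 − 100 = 20 mm Hg. For heart rate, starting from 130:

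- Printed: 173.25 − 130 = 43.25 bpm at age 55, and 204.7 − 130 = 74.7 bpm at 18.
- Bracket moved: 140.25 − 130 = 10.25 bpm at 55, and 171.7 − 130 = 41.7 bpm at 18.

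With the bracket moved, removal still lies above the dosing halt at every eligible age, so the tiers stay in order.

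**Step 5: what escapes.** The 5-minute rule does not act between the two limits: about 172 to 205 bpm at age 18, 153 to 186 at 40, and 140 to 173 at 55. Within that band the 30-minute rule catches any excursion that persists, and the second-occurrence rule catches any repeat. What remains is a first excursion of at least 5 minutes that resolves within 30.

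**Step 6: ceiling on later exposure.** In a session, "The same dose of cocaine, 0mg or 20mg, will be available for all 10 choices on a given day". If the excursion follows the first choice in the 20 mg session, the session resumes, cocaine is chosen every time and no halting criterion is met again, up to 9 × 20 mg = 180 mg could follow. This is an upper bound, not an expected dose.

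**The case against.** The strongest reply is that the protocol never writes 0.85 × (220 − age), so the 33 bpm gap and the proposed limit rest on inference. The protocol calls its removal limits extreme. At age 55 the printed 173.25 bpm fits that description, whereas 140.25 bpm is only about 10 bpm above the routine dosing halt. This stands as a reason to have the limit confirmed clinically. It does not rescue the printed form, because calling a limit extreme does not explain a factor whose only effect is to loosen it.

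The second reply is that other safeguards cover these heart rates. No repeat dose is given above 130 bpm, the next choice is delayed and measures are repeated, and a physician is present until vital signs are normal. The second-occurrence rule runs across the whole protocol and counts blood pressure and behaviour as well as heart rate. This also stands, and it limits the gap to at most one episode per participant. It does not close the gap: the second-occurrence rule presupposes that a participant continues after the first event. Even if a halt were read as ending that session, a participant halted at the first visit would remain eligible for the 20 mg session at the other.

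The third reply is that 180 mg is unrealistic as a measure of harm, since it needs nine further cocaine choices against money rising to $16 with no further breach. That is fair, and the figure should be read only as a ceiling.

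**Conclusion.** The concern holds. The printed removal limit runs from 204.7 bpm at age 18 to 173.25 bpm at 55, and the 0.85 factor works in the wrong direction at every eligible age. That much follows from the printed formula alone. The 33 bpm excess further assumes that 0.85 × (220 − age) was meant. The direction of the factor and the spacing of the tiers both support this, but no text confirms it.

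The consequence is real and narrow: one removal trigger is lost for a first, self-resolving excursion of 5 to 30 minutes. How often that would happen cannot be judged from the document. Because this is an explicit safety threshold, wrong as written and cheap to correct, it should be fixed.

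**What to change.** Rewrite the rule so that a participant is removed when heart rate exceeds 0.85 × (220 − age) bpm for 5 minutes or more. Have the responsible physician confirm that limit, and print the bpm by age beside it (for example 171.7 at 18, 161.5 at 30, 153.0 at 40, 140.25 at 55) so that staff need not calculate it during a session. The 130 bpm dosing halt, the 30-minute rule and the second-occurrence rule can stay as they are.

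The cost is a one-line protocol correction and possibly a few more participants removed.
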